One therapy with the potential to address underlying biological processes responsible for OA pathogenesis is platelet-rich plasma (PRP), an autologous blood product that contains an elevated concentration of platelets. Activation of PRP releases an initial burst then a sustained release of growth factors and other molecules, including platelet-derived growth factor, transforming growth factor-β, type I insulin-like growth factor and vascular endothelial growth factor [11]. Animal studies have shown that these proteins are responsible for a range of critical tissue healing roles such as chondrocyte apoptosis inhibition, bone and vessel remodelling, inflammatory modulation, and importantly, collagen synthesis. Additionally, other bioactive molecules released by platelets, such as fibrin, act as a scaffold and chemo-attractant for further migration of stem and other cells to the damaged tissue [11]. Given the limited repair capacity of articular cartilage, these roles offer a mechanism by which PRP may enhance tissue healing and cartilage regeneration in knee OA.

There is some randomised controlled trial (RCT) evidence about the symptomatic effects of PRP for knee OA. A recent systematic review that included 14 RCTs concluded that PRP was likely to be more effective for pain relief and physical function when compared with control injections that included normal saline, HA or glucocorticoids [12]. However, all RCTs were found to be at a moderate to high risk of bias, and most lacked longer-term follow-up and were inadequately powered with small sample sizes. Only three trials compared PRP to placebo, with results showing significantly greater improvements in symptoms over normal saline at six [13] and 12 months [14, 15]. However, all three studies suffered from major methodological flaws including a lack of adequate blinding suggesting the benefits may have been overestimated. No study has investigated the structural effects of PRP.

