#### Randomisation procedures

Participants will be randomly allocated by telephone to the PRP injection group or the placebo injection group using a randomisation schedule prepared and stored by the National Health and Medical Research Council (NHMRC) Clinical Trial Centre. Randomisation will occur according to a 1:1 allocation ratio in blocks with varying sizes of 6 or 10, stratified according to site (Melbourne or Sydney) and radiographic disease severity (Kellgren and Lawrence grades 2 or 3). At the first treatment appointment, a study nurse will telephone the NHMRC Clinical Trials Centre just before administration of the first injection to reveal the participant’s group allocation.

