#### Interventions

Participants in both the PRP and placebo groups will undergo three intra-articular knee injections performed at weekly intervals, in line with commonly used injection protocols for this condition [16, 22]. The doctor will give the participant the option of having a local anaesthetic injection superficially (subcutaneously) before treatment. The doctor will then check the study knee for the presence of an effusion using ultrasound. If present and deemed to be amenable to aspiration, then this will be performed using a needle inserted in the suprapatellar bursa, and the volume aspirated will be recorded. The study nurse will give the doctor an occluded syringe with a needle containing 5 ml of either normal saline or PRP, and the contents will be injected into the knee joint under ultrasound guidance using a medial patellofemoral approach. Following the injection, passive knee flexion and extension will be performed five times with the participant observed resting for 10 min thereafter.

Participants will return for their second injection approximately 1 week later, and again for a third and final injection approximately 1 week after that. The injection process will be the same as the first injection. After the third injection, participants will be asked about which group they believe they are in, and separately the injecting doctors will also be asked which group they believe the participant is in. After each injection, the study nurse will ask the participant if they experienced any adverse events following the previous injection.

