### Outcome measures

Study outcome measures are presented in Table 1. Our two primary outcome measures are 12-month change in overall average knee pain severity and medial tibial cartilage volume:i)*Average overall knee pain severity*: this will be measured at baseline, 2, 6, 9 and 12 months using an 11-point numeric rating scale (NRS) with terminal descriptors ‘no pain’ (score 0) and ‘worst pain possible’ (score 10). This was chosen because it has well-established clinimetric properties in knee OA and established minimal clinically important differences [24], and is a recommended measure for knee OA RCTs from the Osteoarthritis Research Society International [25].ii)*Medial tibial cartilage volume*: an MRI scan of the study knee will be performed at baseline and 12 months using a 3 T whole body system with a dedicated extremity coil and a T1-weighted fat-suppressed 3D gradient recall acquisition sequence (Additional file 1). Medial tibial cartilage volume will be measured by manually drawing disarticulation contours around the cartilage edges, section by section. To reduce measurement error and bias, one person will measure each participant’s paired set of images, blinded to time sequence and treatment allocation. Regular quality review will occur in 20% of images by a second reader. Our coefficients of variation for these measures are 2.3–2.4% [26].

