
We will also collect a number of additional measures, as well as data regarding participant descriptive characteristics, health services usage and cytokine and growth factor profiles:i)*Additional measures*: these include participant weight, drug/supplement use, adverse events, the success of participant and doctor blinding, use of co-interventions and number of injections.ii)*Descriptive data*: including participant height, body mass index, age, gender, duration of symptoms, radiographic disease severity, knee alignment (measured from the knee x-ray and reported in degrees [34]), current employment, symptom laterality, symptoms in other joints, treatment expectation on a 5 point Likert scale (from “no effect at all” to “complete recovery”), neuropathic pain using the painDETECT questionnaire [35], and physical activity using the Physical Activity Scale for the Elderly (PASE) [36, 37]. The cross-sectional area of the medial tibial plateau from MRI [30] will be measured for use as a covariate.iii)*Health economic evaluation data*: measured using data collected at baseline, and 2, 6, 9 and 12-months. Data include health care costs estimated from healthcare service usage and Quality Adjusted Life Years (QALYs) calculated using the AQoL-8D, and work performance data obtained from the World Health Organisation Health Performance Questionnaire (WHO HPQ) [38].iv)*Cytokine and growth factor concentrations:* aliquots of PRP will be analysed in a subset of participants to determine the concentration of key growth factors and cytokines, such as platelet-derived growth factor, transforming growth factor beta 1, connective tissue growth factor, interleukin 1 receptor agonist, interleukin 1 beta, interleukin 6 and matrix metallopeptidase 9.

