### Statistical analyses

#### Primary analyses

We will conduct an intention-to-treat analysis whereby all participants will be included in the study in the group to which they were randomised. Analysis will be conducted by a biostatistician blinded to treatment group, with two-sided hypothesis tests and *p*-values < 0.05 significant. If the proportion of missing data exceeds 5%, missing outcome data will be imputed using multiple imputation methodology, and sensitivity to the missing at random assumption will be investigated [41]. Changes from baseline will be presented for each group at 2- and 12-month time points using the mean change and 95% confidence intervals. For continuous outcomes (e.g. pain, cartilage volume, physical function), longitudinal analyses will be conducted, with differences in mean change (follow-up minus baseline) compared between the groups using mixed linear regression models with the baseline value, stratifying variables (Kellgren and Lawrence grade and injecting site) and an interaction between month and treatment group as covariates, including random effects for participants [42]. Models including baseline cartilage volume, age, gender, body mass index and cross-sectional area of the medial tibial plateau from MRI [30] will also be fit. Appropriate transformations of outcome measures will be considered if needed to meet statistical assumptions (e.g. linearity, normality and homogeneity of residuals) as assessed using diagnostic plots. Binary outcomes will be compared between groups using risk differences calculated after fitting longitudinal regression models for binary outcomes, adjusted for stratification variables and accounting for clustering of measurements within participants. The other MRI-derived measurements (MOAKS, bone marrow lesion size and cartilage defects) will be compared between groups using appropriate models, adjusting for age, gender, body mass index, and the stratifying variables. The model for cartilage defects will also be adjusted for cross-sectional area of the medial tibial plateau [30]. If appropriate, the effect of PRP on primary outcomes under hypothetical full adherence to assigned treatment will be investigated. The success of blinding will be assessed using the James Blinding Index [43].

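### The only blinding measure named, the James index, pools both arms and credits any 'don't know' answers as blinding; a by-arm index should be added

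*Protocol article*

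**What the plan says.** Under Statistical analyses, Primary analyses, the article gives one sentence on the blinding check: "The success of blinding will be assessed using the James Blinding Index". It sets no cut-off for success and mentions no by-arm index or guess-by-arm table.

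The data come from two sources, described under Interventions. For the first, the article says: "After the third injection, participants will be asked about which group they believe they are in". The second source is the doctor who gave the injections, who makes a guess of their own for each participant. The response options are not given, so the article does not show whether 'don't know' is a permitted answer. Outcome measures lists among the additional measures "the success of participant and doctor blinding, use of co-interventions and number of injections".

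Two other places bear on the weight of the check. One of the two primary outcomes is pain reported by the participant, "using an 11-point numeric rating scale (NRS) with terminal descriptors". And the Background says of the three earlier placebo-controlled trials that "all three studies suffered from major methodological flaws including a lack of adequate blinding suggesting the benefits may have been overestimated".

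**The concern.** The James index has two properties that matter here.

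- **It is pooled.** A single number cannot say which arm guessed correctly. It also cannot separate a belief shared by both arms (most people think they had PRP) from chance guessing in each arm.
- **It gives 'don't know' full credit.** If that answer is available and common, it raises the index and can offset a clear excess of correct guesses among those who do guess.

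At stake is how a difference in self-reported pain is read. If many participants in the PRP arm knew what they had received, a pain difference could partly reflect expectation. A pooled value near or above the random-guessing value of 0.5 could hide this.

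**Working it through.** **Inputs.** The allocation ratio is 1:1 (Randomisation procedures) and 144 participants are to be recruited per arm (Sample size calculations). The article gives no blinding figure to reproduce. All guess shares below are assumptions, including a 'don't know' share of 0%.

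**Formulas.**
- James: BI = [1 + d + (1 - d)K]/2, with K = (P_o - P_e)/P_e. Here d is the overall 'don't know' share, P_o the observed share of wrong guesses among guessers, and P_e the share expected by chance. BI is 0 if all are right, 0.5 under random guessing, and 1 if all answer 'don't know' (or all are wrong).
- Bang, per arm: (right - wrong)/n, with SE = sqrt{[p_r + p_w - (p_r - p_w)²]/n}, where p_r and p_w are the shares of the arm guessing right and wrong.
- With equal numbers of guessers in each arm, P_e = 0.5.

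**1. Shared belief, no 'don't know' answers.** In each arm 108 guess PRP and 36 guess saline. P_o = (36 + 108)/288 = 0.50, so K = 0 and James = 0.50. Bang is (108 - 36)/144 = +0.50 in the PRP arm and (36 - 108)/144 = -0.50 in the saline arm. The pooled value is identical to that of random guessing.

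**2. 'Don't know' answers, same pattern in both arms.** Let c be the share of guessers who are right. Then K = 1 - 2c. For c = 0.8, K = -0.6:

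| 'Don't know' share | James | Bang, each arm: (1 - d)(2c - 1) |
|---|---|---|
| 0% | (1 - 0.6)/2 = 0.20 | 0.60 |
| 37.5% | (1.375 - 0.375)/2 = 0.50 | 0.375 |
| 50% | (1.5 - 0.3)/2 = 0.60 | 0.30 |

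In whole numbers, take 72 'don't know' per arm and 58 of 72 guessers right (81%). James is 0.597 (bootstrap 95% interval 0.54 to 0.65). Bang is 44/144 = 0.306 in each arm, SE 0.053, 95% CI 0.20 to 0.41.

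In general James is at least 0.5 once d ≥ (2c - 1)/(2c). The threshold is 17% for c = 0.6, 29% for 0.7, 37.5% for 0.8, 44% for 0.9 and 50% for 1.0.

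**3. Unblinding in one arm.** Take PRP 86 right, 14 wrong, 44 'don't know', and saline 56, 44 and 44. Then d = 88/288 = 0.306, P_o = 58/200 = 0.29 and K = -0.42. James = (1.306 - 0.694 × 0.42)/2 = 0.507. Bang is 72/144 = 0.50 (PRP) and 12/144 = 0.08 (saline).

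**4. Where the index does respond.** With no 'don't know' answers, PRP guessers 90% right and saline at chance, P_o = (0.10 + 0.50)/2 = 0.30, K = -0.40 and James = 0.30. With 20% 'don't know' in each arm and the same guessing, James = (1.2 - 0.32)/2 = 0.44.

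**The case against.** The strongest objection is that the 'don't know' mechanism rests on something the article does not state. If participants must choose a group, 80% correct guessing gives James 0.20, a plain signal of unblinding, and that half of the concern falls away. This stands, and is why the shares above are labelled as assumptions. The pooling limitation does not depend on it.

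A reader might go further than the document allows in four ways.

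- That the James index cannot detect unblinding in one arm. It can: step 4 gives 0.30 and 0.44. It cannot say which arm is affected, and it may mask the problem when 'don't know' is common.
- That the trial will declare blinding successful above 0.5. No cut-off is set; 0.5 is used here only as the random-guessing value.
- That better blinding is the trial's main claimed advantage. The Background names inadequate blinding as one flaw among others, and the Discussion also stresses the scarcity of placebo controls and the absence of structural outcomes.
- That a by-arm index would settle whether expectation explains a pain difference. Neither index estimates an expectation effect; by-arm figures only show where correct guessing occurred.

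It is also fair to say that blinding rests mainly on design. Blood is drawn in both arms, syringes are prepared in a separate room and their contents are covered. The MRI outcome is read blind to allocation and time sequence. Finally, an analysis plan that is not shown may already add a by-arm summary, so the James index is the sole measure only as far as this article goes. Even so, the article makes a specific choice of measure, and that choice can be improved.

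**Conclusion.** The point holds as a low-severity, free improvement. The named measure is a recognised one, and nothing in the article is contradictory or miscalculated. Used alone, however, it can equal 0.50 when the by-arm values are +0.50 and -0.50. If 'don't know' is offered, it can reach 0.60 with about 80% of guessers right. The first result needs no assumption about response options, only an assumed guessing pattern. The second needs 'don't know' to be both available and frequent. The documents do not support concluding that blinding will fail or that the pain result will be biased; the claim is only that this measure alone could give false reassurance.

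**What to change.** Keep the James index. Add, before unblinding:

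- the Bang index with 95% confidence interval for the PRP and saline arms, separately for participants and for injecting doctors;
- the guess-by-arm table for each group of respondents, including any 'don't know' answers;
- a statement of the response options used;
- a statement that blinding will be interpreted from these results together, not from the pooled value alone.

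The guesses are already being collected, so the cost is a few lines in the analysis plan and in the code. No new data and no change to trial conduct are needed. Fixing it in advance also prevents the choice of index from appearing to follow the results.

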#### Moderator analyses

We will also conduct planned exploratory analyses to investigate potential moderators that could influence response to treatment at 12 months. Pre-identified potential moderators include KL grade, body mass index, knee effusion on MRI and knee alignment. A description of the hypothesis for each moderator analysis and the rationale is found in Additional file 2. To assess the moderation of the effect of randomised treatment group by binary potential moderators (KL grade and effusion), an interaction term between randomised group and the potential moderator, as well as terms for the randomised group and the potential moderator, will be included in outcome regression models. To assess the moderation of the effect of randomised treatment group by continuous potential moderators (body mass index and knee alignment), the multivariable fractional polynomial interaction approach described previously [44] will be applied. This approach allows for nonlinear functional forms of the continuous potential moderator to be included in the regression model for outcomes, with the potential for separate nonlinear functional forms in each treatment group.

#### Economic analyses

The cost-effectiveness of PRP will be estimated by calculating the incremental average health care cost of those treated and the difference in pain score and health-related quality of life over the 12 months of the trial compared to the placebo group. The comparison will be reported as the incremental cost per unit change in the pain score, the incremental cost per additional quality-adjusted life year, and the net benefit of treatment at 12 months. The quality-adjusted life year will be calculated using the average AQoL-8D value. Net benefits will be calculated using a range of potential money values of a quality-adjusted life year. Costs will include the cost of treatment and associated imaging as well as the downstream medical, pharmaceutical and hospital costs in each arm. Health care utilisation data will be collected by questionnaire. Cost-effectiveness will be calculated using separate generalised linear regression models for costs and outcomes controlling for baseline levels. Predicted costs and outcomes will be used to calculate means for cost-effectiveness ratios and net benefits with bootstrapped 95% confidence intervals. If there is no demonstrated benefit from PRP, we will calculate the incremental average health care cost of those treated. In the secondary economic analysis, the impact on employment and productivity at work will be calculated from data collected by questionnaire.

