**Methods:**

This will be a two-group, superiority, randomised, participant-, interventionist- and assessor-blinded, placebo-controlled trial. Two hundred and eighty-eight participants aged over 50 years with painful knee OA and mild to moderate structural change on x-ray (Kellgren and Lawrence grade 2 and 3) will be randomly allocated to receive either three PRP injections or three normal saline injections into the knee joint at weekly intervals. The primary outcomes will be 12-month change in average overall knee pain severity (numeric rating scale) and medial tibial cartilage volume (magnetic resonance imaging (MRI)). Secondary outcomes include additional measures of knee pain and other symptoms, function in daily living and sport and recreation, quality of life, participant-perceived global ratings of change, and other MRI structural outcomes including meniscal and cartilage morphology, synovitis, effusion, bone marrow lesions and cartilage defects. A range of additional measures will be recorded, and a separate health economic evaluation will be performed.

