Heterogeneity in the preparation and injection methods used by published studies has also limited the ability to determine optimal PRP protocols. However, protocol characteristics of those RCTs that have reported positive effects on pain and function have generally utilised a single centrifugation at a slower speed (approximately 1500 g) for approximately 5 min to yield leucocyte poor PRP, and injected fresh PRP (i.e. not frozen and then thawed for subsequent injections) over 3 injections at weekly intervals [16]. There is some preliminary evidence to suggest younger patients, and those with less severe radiographic disease may experience greater symptomatic benefits [14, 17–19].

The primary aim of this two-arm randomised, placebo-controlled trial is to determine if a series of injections of PRP into the knee joint leads to significantly greater reductions in average knee pain severity and less loss of medial tibial cartilage volume when compared to placebo saline injections over 12 months in people with symptomatic knee OA. The secondary aim is to determine if PRP has significantly greater benefits for other clinical (other knee pain measures, physical function, quality of life, participant global rating of change) and magnetic resonance imaging (MRI) structural outcomes (effusion, synovitis, cartilage morphology, bone marrow lesions, cartilage defects, meniscal morphology) compared to placebo injections at 2 (clinical) and 12 (clinical and MRI) months. We will also conduct an embedded economic evaluation of PRP if benefits are found.

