The following secondary outcome measures will also be collected:i)*Average knee pain severity during walking*: measured at baseline, 2 months and 12 months on an 11-point NRS, where 0 indicates no pain and 10 indicates worst pain possible.ii)*Intermittent and Constant Osteoarthritis Pain (ICOAP) questionnaire:* measured at baseline, 2 months and 12 months. This is a self-report multi-dimensional, OA-specific measure of pain experience, with established reliability, internal consistency and validity in people with knee OA [27]. It is comprised of 5-items assessing constant knee pain in the previous week, and 6-items assessing intermittent knee pain in the previous week. Questions regarding pain intensity have terminal responses of ‘not at all’ (score 0) and ‘extremely’ (score 4), and questions regarding pain frequency have ‘never’ (score 0) to ‘very often’ (score 4). Total scores range from 0 to 100, with higher scores indicating worse pain.iii)*Knee Injury and Osteoarthritis Outcome Score:* measured at baseline, 2 months and 12 months. This is a knee-specific self-report outcome measure with high test-retest reliability, internally consistent and face and content validity [28, 29]. Likert responses range from None to Extreme, and scores range from 0 to 100, with lower scores indicating worse symptoms, function or quality of life. It is comprised of the following five subscales:Pain: scored from 9 questions about knee pain frequency experienced in the last week, and the amount of knee pain experienced during specific activities such as twisting, bending and walking.Other symptoms: scored from 7 questions regarding other symptoms experienced in the last week, such as swelling, restricted range of motion and mechanical symptoms.Function in daily living: scored from 17 questions regarding knee function in the last week.Function in sport and recreation: scored from 5 questions regarding function with sport and recreational activities in the last week.Knee-related quality of life: scored from 4 questions about knee-related quality of life experienced in the last week.iv)*Participant-perceived global ratings of change:* participants will rate perceived overall change with treatment (compared to baseline), and change in pain and physical function, on a 7-point Likert scale (from “much worse” to “much better”) at 2 and 12 months [30]. Those ‘moderately better’ or ‘much better’ will be classified as improved. All other respondents will be classified as not improved.v)*Health-related quality of life:* measured at baseline, 2 months and 12 months using the 35-item Assessment of Quality of Life (AQoL-8D) instrument [31]. The AQoL-8D has strong psychometric properties and is more responsive than other widely-used scales [32]. Scores range from − 0.04 to 1.00, with higher scores indicating better quality of life. The AQoL-8D will also be measured at 6 and 9 months for the health economic evaluation.vi)*Other MRI-derived measurements*: using a 3 T whole body system with a dedicated extremity coil and a T1-weighted fat-suppressed 3D gradient recall acquisition sequence (Additional file 1). Outcomes include:MRI osteoarthritis knee score (MOAKS): an OA-specific semi-quantitative tool evaluating multi-feature joint changes associated with OA [33]. We will assess the following subscores: meniscal morphology (any regions with worsening at 12 months compared to baseline; scored as yes or no); inter-condylar synovitis (worsening in inter-condylar synovitis at 12 months compared to baseline; scored as yes or no); cartilage morphology (number of areas with worsening in thickness at 12 months compared to baseline; categorised as 0, 1, 2, or 3+); and whole knee effusion (change in whole knee effusion at 12 months compared to baseline; categorised as worsened, no change or improved).Bone marrow lesion size: assessed from the MRIs at baseline and 12-months using categorical scoring in the medial distal femur and the proximal tibia (range 0–3 per region, with higher scores indicating greater bone marrow lesion size). Progression of bone marrow lesions (yes/no) will be defined as an increase in score by at least 1 from baseline to follow-up in either the medial tibial or medial femoral compartment.Cartilage defects: score in the medial distal femur and the proximal tibia at baseline and 12-months using categorical scoring (range 0–4 per region, with higher scores indicating greater cartilage defects). Progression of medial cartilage defects (yes/no) will be defined as an increase in score by at least 1 from baseline to follow-up in either the medial tibial or medial femoral compartment.

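### Cost per QALY and net benefit depend on an undefined demonstrated benefit, although the abstract promises the economic evaluation without condition

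*Protocol article*

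**What the plan says.** Three places in the protocol article describe whether the economic evaluation takes place:

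- Abstract, Methods: "a separate health economic evaluation will be performed". There is no condition.
- Background, last paragraph: "We will also conduct an embedded economic evaluation of PRP if benefits are found".
- Economic analyses: the section plans incremental cost per unit of pain score, incremental cost per QALY, and net benefit over a range of money values for a QALY. These come from regression models that control for baseline, with bootstrapped 95% confidence intervals. It then adds: "If there is no demonstrated benefit from PRP, we will calculate the incremental average health care cost of those treated".

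The data are collected whatever the result. The Outcome measures section says the economic data are "measured using data collected at baseline, and 2, 6, 9 and 12-months", and gives the reason for two of the AQoL-8D assessments: "The AQoL-8D will also be measured at 6 and 9 months for the health economic evaluation".

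On the QALY itself, the Outcome measures section has "Quality Adjusted Life Years (QALYs) calculated using the AQoL-8D", and the Economic analyses section has "The quality-adjusted life year will be calculated using the average AQoL-8D value". The latter frames the comparison as "the difference in pain score and health-related quality of life over the 12 months of the trial". Neither section says which visits enter the average or how they are weighted.

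**The concern.** Whether cost-effectiveness is reported depends on a result that will be known by then. The rule names no outcome and no threshold for benefit. With two primary outcomes, the trigger could be pain, cartilage volume, either, both, or the QALY difference itself. The choice could therefore be made after the results are seen.

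The condition also fits badly with the method it restricts. Net benefit with a bootstrap interval is meant for effects that are small or uncertain, and needs no prior significance. A non-significant difference in pain or cartilage is not a QALY difference of zero. At stake is whether a trial that collects costs and utilities at five time points answers its cost-effectiveness question when the primary results are null.

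**Working it through.** **Step 1. What would be reported, by result**

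| Place | Benefit demonstrated | No benefit demonstrated |
|---|---|---|
| Abstract | economic evaluation | economic evaluation |
| Background | economic evaluation | none implied |
| Economic analyses | incremental cost, cost per pain unit, cost per QALY, net benefit | incremental cost only |

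The three places agree only in the first column. In the second, incremental QALYs, net benefit and the joint uncertainty of cost and effect are missing from the detailed plan.

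**Step 2. How much selection on significance could matter**

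The article gives no figure for the economic analysis, so the only power figures are those under Sample size calculations. They reproduce:

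- Cartilage: difference 0.40 × 2.8 = 1.12; SD 3.5; correlation 0.50. n = 2 × (1.960 + 0.842)² × 3.5² × (1 − 0.50²) / 1.12² = 115 per arm, and 115 / 0.80 = 144 after loss to follow-up.
- Pain: difference 1.8; adjusted SD 2.4 × √(1 − 0.29²) = 2.297. With 115 per arm, power is 99.99%, which agrees with the stated figure of over 99%.

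Assume that benefit means two-sided p < 0.05 in favour of PRP on one outcome (the article does not say so). For a normal estimate with power p, let z be the standard normal quantile of p, φ the standard normal density, and θ = 1.960 + z. Then

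mean estimate given significance / true effect = 1 + φ(z) / (p × θ)

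- p = 0.80: 1 + 0.280 / (0.80 × 2.802) = 1.12
- p = 0.99: 1 + 0.0267 / (0.99 × 4.286) = 1.01
- p = 0.50 (an assumption, to show the range if the true effect is smaller than designed): 1 + 0.399 / (0.50 × 1.960) = 1.41

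These factors apply to the outcome that triggers the report. They pass to the QALY gain only as far as QALYs correlate with that outcome.

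**Step 3. What the average AQoL-8D value could mean**

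Visits at 0, 2, 6, 9 and 12 months leave intervals of 2, 4, 3 and 3 months. The trapezoidal weights are 2/24, 6/24, 7/24, 6/24 and 3/24, which sum to 1. Over one year the area under the curve is therefore the time-weighted average. For a gain d that is zero at baseline and constant from month 2:

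- time-weighted: (6 + 7 + 6 + 3)/24 = 22/24 = 0.917d
- unweighted mean of five visits: 4/5 = 0.800d; ratio 0.800/0.917 = 0.873, that is −12.7%
- unweighted mean of four follow-ups: 1.000d; ratio 1.000/0.917 = 1.091, that is +9.1%

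Other time courses change both size and direction. For the five-visit mean the ratio is 0.76 if the effect is full at month 2 and fades to zero at month 12, 0.97 if it builds linearly over 12 months, and 1.01 if it is zero at month 2 and rises to month 12. With no effect at any visit, every rule gives zero.

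**The case against.** The condition has a reason behind it: a cost per QALY for a treatment that does not work is of little use, and a ratio with a denominator near zero is unstable. The evaluation is reduced, not dropped, because incremental cost is still reported. AQoL-8D is a secondary outcome at 2 and 12 months in any case, so quality-of-life results will appear. The article calls the economic evaluation separate, and a fuller plan may define benefit and the QALY rule.

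Much of this stands. Instability is a fair reason not to lean on the ratio, but net benefit does not share that weakness and is already planned. The secondary AQoL-8D comparison does not replace incremental QALYs set jointly against cost. A fuller plan may supply detail, but the condition is a rule that this article states, and the Abstract and Background disagree about it.

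A reader might infer two stronger points. The first is that the condition biases the economic estimate. It does not: it decides which summaries are reported, and the estimate from the trial data is the same either way. The second is that QALYs will be miscalculated because the visits are unevenly spaced. The article does not say the average is unweighted. A time-weighted average is the correct 12-month quantity, and the framing over the 12 months of the trial fits it. Naming the rule is detail that an article may leave out.

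**Conclusion.** The condition is a real fault of reporting in a secondary analysis. As written, cost per QALY and net benefit appear only after a favourable result on an undefined criterion, and a null trial reports incremental cost alone.

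Inflation from this selection is about 12% if the trigger is significance on cartilage at the planned 80% power, and about 1% or less if it is pain at the assumed 1.8-unit difference. Both figures assume a p < 0.05 rule and concern the triggering outcome, not the QALY gain. The effect on QALYs cannot be sized from the article.

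The QALY sentence is ambiguous, not shown to be wrong. The −12.7% holds only for an unweighted five-visit mean and an effect constant from month 2. Primary outcomes and sample size are unaffected.

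**What to change.** This is a cheap improvement.

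1. In the Background, remove the condition at the end of the sentence on the economic evaluation.
2. In Economic analyses, remove the branch for no demonstrated benefit. State instead that incremental cost, incremental QALYs and net benefit, with bootstrapped 95% intervals, will be reported whatever the primary results. The Abstract, Background and Economic analyses then agree, and benefit no longer needs a definition for this purpose.
3. As a clarification only, say that the average AQoL-8D value is the time-weighted average: the trapezoidal area under the curve over 0, 2, 6, 9 and 12 months, with the baseline adjustment already planned.

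The cost is wording, plus slightly more analysis if the trial is null. No new data are needed. The change should be made before unblinding, so that neither the reporting rule nor the averaging rule can be chosen in the light of the results.
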